UMIN University Hospital Medical Information Network

UMIN-CTR UMIN Clinical Trials Registry UMIN Clinical Trials Registry

**1. Outline of the Study**

To investigate the effects of wearing blue light-cut glasses before bedtime on melatonin levels, sleep, and diurnal rhythms in school children.

Principal Investigator [name], Professor, Department of Psychiatry, Stanford University School of Medicine, and Director, Sleep and Biological Rhythms Laboratory, Stanford University

Study Design Prospective, randomized, sham-controlled, single-blind, crossover, exploratory study

Study Apparatus Blue light cut glasses

Endpoints Primary endpoint: Evaluation of salivary melatonin concentration

Secondary endpoints:

1. assessment of circadian rhythm

2. assessment of sleepiness, mood, and motivation (modified version of the NRS scale for sleep)

3. assessment of sleep quality and quantity (Children's Sleep Questionnaire for Elementary School Children/Chronotype Assessment)

Study subjects

Target number of cases School children with a habit of exposure to blue light before bedtime, 40 cases

Eligibility criteria [Selection criteria

(1) Healthy elementary school boys aged 9-12 years at the time of obtaining consent

(ii) Those who regularly use glasses with vision correction in daily life

(iii) Those who are habitually exposed to blue light from LED displays, etc. for an average of one hour or more per day before bedtime.

(4) Those who have obtained written consent for participation in this study from themselves and their parents or guardians.

Exclusion criteria

(1) Those who use the following lenses, which cannot be made according to the specifications of the lenses to be used in this study, in their regular glasses in daily life.

(1) Those who use the following lenses, which cannot be made according to the specifications of the lenses used in this study, in their regular spectacles for daily use

CYL: -4.00 to 0D, distance vision SPH: 0 to +4.00D, CYL: 0 to +4.00D) or lenses other than single vision lenses such as progressive or prismatic lenses

(ii) Those who are aware that the power of the spectacles they regularly use in their daily lives is not appropriate and need to have their power re-measured at a hospital or ophthalmologist's office, etc.

(iii) Those whose lenses of eyeglasses they regularly use in their daily lives cannot be checked at eyeglass stores, etc. (iv) Those whose lenses are not suitable for sleep, autonomic nervous system, central nervous system, etc.

(iv) Those who are taking drugs or supplements that affect sleep, autonomic nerves, or central nervous system.

(v) Those who have a history of or are suffering from sleep disorder, psychiatric disease, immune/allergic disease, metabolic disorder, corneal disorder, retinal disorder, dry eye, eye strain, etc. (vi) Those who are taking medicines for hay fever, etc.

(vi) Those who need drug treatment for hay fever, etc.

(vii) Persons with infectious diseases stipulated in the Infectious Diseases Control Law and blood-borne diseases (HBV, HCV, HIV, syphilis) (including persons in close contact)

(viii) Persons who cannot properly wear the examination equipment under the supervision of a person with parental authority before going to bed.

(ix) Persons with irregular sleeping habits

(x) Persons who plan to change their living environment during participation in the research.

(xi) Any other person who is deemed inappropriate as a research subject by the physician.

Research period: From the date of approval by the Ethical Review Committee to September 2022.

Period of case registration: From the date of approval by the Ethics Review Committee to June 2022

Research Category Ethical Guidelines for Life Sciences and Medical Research Involving Human Subjects

Funds/test equipment

Provider Jinz Holdings, Inc. 2.

In recent years, the increase in the number of children with so-called "developmental disabilities" among school-aged children has become a social issue. According to the "Results of the Survey on the Status of Implementation of Instruction through Classroom Instruction for the Fiscal Year 2028" conducted by the Ministry of Education, Culture, Sports, Science and Technology, the number of children receiving instruction through classroom instruction is 134,185, more than double the 54,021 students in 2009, 10 years ago. The number of students with Attention Deficit Hyperactivity Disorder (ADHD) has increased particularly markedly, from 4,013 in FY2009 to 24,709 in FY 2019, an increase of more than five times. The rapid increase in ADHD, learning disabilities, autism, and emotional disorders over the past 10 years can be seen as a reflection of the loss of mental stability among children. This can be seen as a reflection of the fact that children's mental stability has been deteriorating, and it is necessary to take some measures for their healthy development.

On the other hand, the time spent on the Internet by the public, including children, has increased significantly in recent years due to faster Internet speeds and the spread of smartphones and tablet terminals. According to the "2049 Internet Use by Youth Survey (Preliminary Report)" conducted by the Cabinet Office, among the groups that responded to the survey, 35.5% of 2-year-olds use the Internet, 50.2% of 3-year-olds use the Internet, and more than 70% of 8-year-olds and older use the Internet. The average daily usage time was 67.4 minutes for 2-year-olds, 88.8 minutes for 3-year-olds, and 97.4 minutes for 8-year-olds, indicating that the main purposes are watching videos and playing games. In the results of the 2027 survey, the average duration of Internet use increased from 56.9 minutes to 97.4 minutes for 8-year-olds, for example2).

This survey on Internet use by youth began in FY2009, and in the first year of the survey, the average daily Internet use by elementary school students using computers was 24.8 minutes, and 25.5 minutes by junior high school students, while the percentage of elementary school students owning cell phones was only 21 3). In the last decade, the rate of Internet use among elementary school students has more than tripled, and the average time spent on the Internet has increased by about four times.

In light of the above findings, it is undeniable that the expansion of Internet use has shortened the sleeping hours of children, leading to a shift in their daily rhythm to a nocturnal lifestyle, which in turn has led to a decline in schoolwork and social activity, and eventually to truancy. It is also thought that biochemical factors, such as hormone disruption, may be behind this.

Viewing videos via the Internet is usually done through electronic device displays. Currently, LCD monitors are the main type of display in electronic devices, and LEDs are mainly used as the light source for backlighting. Most of the current white LEDs are used as a white light source by absorbing light from blue LEDs into a yellow phosphor to emit yellow fluorescence, which is then mixed with the original blue light. This results in the light emitted by electronic device monitors having a higher intensity of blue light, or "blue light," compared to the visible region of normal sunlight4).

Recently, it has been shown that photoreceptors that respond to the wavelength of "blue light" called ipRGCs (intrinsically photosensitive Retinal Ganglion Cells) exist in the retina of the human eye, and that nerve stimulation from these receptors causes the optic chiasmatic nucleus (OCN) in the brain to be activated by blue light. Neural stimulation from these receptors affects the production of hormones such as melatonin via the suprachiasmatic nucleus and pineal gland in the brain, and is consequently related to the human circadian rhythm4). Recent studies have also shown that there is a bidirectional relationship between ADHD and sleep disorders. In other words, sleep disorders are not only a factor in the onset of ADHD or an aggravating factor in ADHS, but are often associated with various sleep disorders in ADHD, and it has been pointed out that improvement of sleep disorders may lead to prevention of ADHD onset and improvement of symptoms5). Recently, a melatonin preparation has been approved in Japan for the improvement of sleep onset difficulties associated with childhood neurodevelopmental disorders. This is a replacement therapy that is expected to have therapeutic effects on neurodevelopmental disorders by improving sleep disturbances and diurnal rhythms through the administration of endogenous melatonin6).

Based on these findings, we believe that the disruption of children's circadian rhythms due to exposure to blue light at night from the use of smartphones and tablets may cause children to shift their lives to a nighttime pattern, preventing them from getting proper sleep, and contribute to the risk of developing mental and physical disorders in children, which have been on the increase in recent years. In this study, melatonin concentration, which is directly involved in circadian rhythm,7) will be used as an indicator of the effect on circadian rhythm, and a sham-controlled comparative study will be conducted to examine whether the use of glasses that block blue light increases melatonin concentration before and after bedtime and has a positive effect on sleep and diurnal rhythm. As a secondary evaluation, sleep and wake time will be measured with an actigraph, and sleep-related quality of life will be quantified through a questionnaire for study subjects to evaluate the effects of blue light cutoff on sleep quality, diurnal rhythm, daytime concentration, and mood.

If the effects of blue light on children's circadian rhythm and sleep quality are clarified through this study, it is expected to help in the treatment of mental and physical disorders and disorders, including ADHD, in children, which have been increasing in recent years.

6. objective

To examine whether wearing blue light-cut glasses before and after bedtime increases melatonin levels in school children who are habitually exposed to blue light before bedtime, and whether this has a positive effect on their sleep and diurnal rhythm.

7. study design

Prospective, randomized, sham-controlled, single-blind, crossover, exploratory study

8. study subjects and target number of subjects

School children with a habit of exposure to blue light before bedtime, 40 cases

9. study period

Research period: From the date of approval by the Ethical Review Committee to September 2022

Period of case enrollment: Ethics Review Committee approval date - June 2022

10. research methods

10.1 Research Procedures

10.1.1. Schema

[figure not shown]

10.1.2. Study Schedule

Before the start of the study Prior wearing period Non-wearing period Switching wearing period End of the study (discontinuation)

1: Conducted voluntarily on the day before the first day of use, but no information will be collected.

2: Questionnaires will be administered by a person with parental authority to the research subjects.

3: Sleep/wake information will be collected daily at bedtime during the period of use.

10.1.3. Explanation of the study, obtaining consent, and assent

The principal investigator(s) will explain the study to the potential research subjects (school children) and their parent or guardian using the "Assent Document" (Appendix A) and the "Explanatory Document" (Appendix B), and will obtain free and voluntary consent for participation in the study from the potential research subjects (school children) themselves and their parent or guardian using the "Consent Document". Consent. In this study, the consent of only a surrogate consentor is not acceptable.

Methods of Dialogue

Prior to the confirmation of eligibility, the principal investigator (or subinvestigator) will distribute by mail the "Assent Document" for school children and the "Explanatory Document" for their parent or guardian, which have been approved by the Ethics Review Committee, to the potential research subjects themselves and their parent or guardian, and will fully explain the research orally to the participants using the web conferencing system. After explaining the research, the potential research subjects themselves will be approached to participate in the research after confirming that they have fully understood the content of the research, and the free and voluntary consent of the potential research subjects themselves and their parent or legal guardian will be obtained in writing using the "Consent Form".

If they agree to participate in the research, the potential research subject and the person with parental authority sign the consent form, enter the date of consent, and send it by mail to the physician in charge who provided the explanation. The physician in charge (including the research collaborator if the research collaborator provided supplementary explanations) will write the date of explanation and affix his/her name and seal or sign the consent form. The original consent form signed by the explainer will be kept by the principal investigator, and a copy will be mailed to the research subject. The research subject will keep a copy of the consent form sent to him/her.

If the research subject and the person with parental authority wish to withdraw consent, the research subject and the person with parental authority will fill in the date of withdrawal of consent on the "Consent Withdrawal Form" and sign it. In addition, the physician in charge and the research collaborator will fill in the date of explanation and affix their names and seals or sign the form. Two copies of the consent form and the withdrawal of consent form (if the research subject and the person with parental authority wish to withdraw consent) will be made, one copy will be mailed to the research subject and the person with parental authority, and one copy will be kept in the case file for the study.

10.1.4. Confirmation of Eligibility

The principal investigator will check the eligibility (selection and exclusion criteria) of research subjects who have given their consent to participate in this study. See "11. Selection of Research Subjects" for selection and exclusion criteria. 10.1.5.

10.1.5 Enrollment and Assignment

Study subjects will be randomly assigned to the "blue light cut glasses pre-fit group" and the "Siamese glasses pre-fit group" in a ratio of 1:1. Assignment will be made at the time of registration in the Web Registration Assignment System. Although the first pair of spectacles to be worn will be specified, the results of the individual allocation for each subject will not be communicated.

10.1.6. Survey Methods and Items

The study will be conducted in the home of the research subjects under the supervision of their custodians. Among the potential research subjects who have applied to the recruiting company, the study will be conducted on those research subjects who have given written explanation of the study to the potential research subjects, obtained written consent and assent, and meet the eligibility criteria.

During the study, the study subjects will be instructed to lead a normal life, but to disable the blue light cut mode (night mode, night mode, etc.) on the LED display electronic terminal in consideration of its impact on the study results.

The first wearing of the test spectacles will be on the 1st day and will be completed on the 14th day. The first day of wearing the test spectacles shall be Day 1 and shall be completed on Day 14, and the switching of the spectacles shall be started on Day 22 and completed on Day 35. The first day of the test (Day 1 and Day 22) should be a Friday. In addition, an optional short wearing practice session may be conducted on the day prior to Day 1.

From Day 1 to Day 14 of the prior wearing period, the blue light cut glasses prior wearing group will wear blue light cut glasses and the Siamese glasses prior wearing group will wear Siamese glasses for approximately 3 hours before bedtime every day (14 days of wearing period). Days 15 to 21 will be a non-wearing period for each group, during which the subjects will wear their regular eyeglasses. From Day 22 to Day 35 of the switching period, the subjects in the blue light-cut glasses-first group will wear Siamese glasses, and those in the Siamese glasses-first group will wear blue light-cut glasses for approximately 3 hours before bedtime every day (for 14 days). The test spectacles will be made with the same power as the spectacles that each subject wears in his/her daily life.

During the period of wearing the test spectacles, changes in sleep-wake rhythm will be recorded using an actigraph, and saliva samples will be collected by the research subjects themselves on the day before the start of wearing the spectacles, on the 7th, 14th, 28th and 35th days after the start of wearing, and questionnaires will be administered on the 8th, 15th, 29th and 36th days after the end of wearing the spectacles.

A sleep diary will be filled out daily during the period from Day 1 to Day 36.

10.1.6.1. background information on study subjects

The following items will be surveyed at the time of case enrollment to confirm eligibility

(1) Age (at the time of obtaining consent), gender, area of residence, information on the power of eyeglasses regularly used in daily life, environment of exposure to blue light, etc.

(2) Degree of sleep disturbance

The degree of sleep disturbance of each research subject will be confirmed using the Children's Sleep Questionnaire for Elementary School Children (Appendix C) by Mihoshi et al.8) . The Elementary School Children's Sleep Questionnaire was designed to assess sleep status during the last month using 9 categories (I RLS; restless legs syndrome, II excessive daytime sleepiness, III OSAS; obstructive sleep apnea syndrome, IV daytime behavior, V morning symptoms, VI Sleep duration, VII Insomnia/rhythm, VIII Sleep habits, IX Sleep rhythm on holidays). (1) Not at all applicable, (2) Not applicable, (3) Somewhat applicable, (4) Somewhat applicable, (5) Applicable, (6) Very applicable Responses within 3 months prior to case registration are considered acceptable.

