The time of sleeping and waking, time of use of devices emitting blue light, status of blue light cut mode setting (including protective film status), etc. shall be recorded.

10.2. test equipment

The following products shall be used as the test spectacles. For both blue light cut spectacles and Siamese spectacles, the power of vision correction shall be equivalent to that of the spectacles regularly used by the research subjects in their daily lives.

(1) Eyeglass frames (for both blue light cut glasses and Siamese eyeglasses)

KUF-20S-113~120 Slim Airframe-Kids Basic made by JINS

(2) Eyeglass lenses

［Blue light cut glasses]

JINS SCREEN lens HEAVY made by JINS (blue light cut rate 40%@EN standard)

［Siamese eyeglasses]

Standard clear lenses manufactured by JINS

11. selection of study subjects

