11.1 Selection and Exclusion Criteria

Among school children who have a habit of being exposed to blue light before bedtime, those who meet the following selection criteria and do not violate the exclusion criteria will be included in the study.

(1) Selection criteria

(1) Healthy elementary school boys aged 9-12 years at the time of obtaining consent

(ii) Those who regularly use glasses with vision correction in daily life

(iii) Those who are habitually exposed to blue light from LED displays, etc. for an average of one hour or more per day before bedtime.

(iv) Those who have obtained written consent for participation in this study from themselves and their parent or guardian.

(2) Exclusion criteria

(1) Those who use the following lenses, which cannot be made according to the specifications of the lenses used in this study, in their regular eyeglasses in daily life.

Lenses with power that falls outside the following ranges (myopia: SPH: -8.00 to 0D, CYL: -4.00 to 0D, hyperopia: SPH: 0 to +4.00D, CYL: 0 to +4.00D) or lenses other than single vision lenses such as progressive or prismatic lenses

(ii) Those who are aware that the power of the spectacles they regularly use in their daily lives is not appropriate and need to have their power re-measured at a hospital or ophthalmologist's office, etc.

(iii) Those whose eyeglass lenses used regularly in daily life cannot be checked by eyeglass stores.

(iv) Those who are taking drugs or supplements that affect sleep, autonomic nerves, or central nervous system.

(v) Those who have a history of or are suffering from sleep disorder, mental disorder, immune/allergic disease, metabolic disorder, corneal disorder, retinal disorder, dry eye, eye strain, etc. (vi) Those who are taking medication for hay fever, etc.

(vi) Those who need drug treatment for hay fever, etc.

(vii) Persons with infectious diseases stipulated in the Infectious Diseases Control Law and blood-borne diseases (HBV, HCV, HIV, syphilis) (including persons in close contact)

(viii) Persons who cannot properly wear the examination equipment under the supervision of a person with parental authority before going to bed.

(ix) Persons with irregular sleeping habits

(x) Persons who plan to change their living environment during participation in the research.

(xi) Other subjects who are deemed inappropriate as research subjects by the physician.

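### Software blue-light-cut modes are switched off, but filtering screen films may stay on, and filtering everyday glasses are neither excluded nor asked about by name

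*Protocol*

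**What the plan says.** **Screens.** Section 10.1.6 asks the children to live normally but "to disable the blue light cut mode (night mode, night mode, etc.) on the LED display electronic terminal", and gives the possible effect on the results as the reason. The diary item in 10.1.6.5 groups films with these modes: "status of blue light cut mode setting (including protective film status), etc. shall be recorded". Nothing tells families to remove a film. The diary runs from Day 1 to Day 36.

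**Everyday glasses.** The lens-related exclusions in section 11.1 cover four things: power outside a stated range, "lenses other than single vision lenses such as progressive or prismatic lenses", power the child knows to be unsuitable, and "Those whose eyeglass lenses used regularly in daily life cannot be checked by eyeglass stores". None refers to blue-light filtering. Inclusion criterion (iii) asks that the child be "habitually exposed to blue light from LED displays, etc. for an average of one hour or more per day before bedtime" and does not mention filters. The enrolment survey in 10.1.6.1 collects "information on the power of eyeglasses regularly used in daily life, environment of exposure to blue light, etc"; a filter or coating on the regular lenses is not named.

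**What is worn when.** Study spectacles are worn for about three hours before bed on Days 1 to 14 and 22 to 35. "The test spectacles will be made with the same power as the spectacles that each subject wears in his/her daily life". Between the two periods, "Days 15 to 21 will be a non-wearing period for each group, during which the subjects will wear their regular eyeglasses".

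**Lenses and sampling.** Section 10.2 gives a 40% blue-light cut for the active lens and a standard clear lens for the sham. Saliva is taken the evening before the start and on Days 7, 14, 28 and 35, at 3, 2 and 1 hours before bed and just before bed (10.1.6.3).

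**The concern.** By switching off night modes, the protocol accepts that filtering already present can distort the comparison. It then leaves two other routes open.

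A filtering film acts under both lenses, so the active lens has less screen blue light to remove. If melatonin responds to the amount of light removed, the expected difference shrinks. The trial has 40 children and, by section 14.3, no power calculation, so there is no known margin to absorb this.

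For a child whose regular glasses filter blue light, the week meant to separate the two conditions is spent in a filter. The pre-study sample is then probably not an unfiltered reference either. Such a child also fits poorly with the objective in section 6, which concerns children with habitual evening exposure.

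**Working it through.** The protocol states no figure on this point, and no power, effect size or standard deviation. There is nothing to reproduce, so what follows is a comparison of the provisions and an illustration on stated assumptions.

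**1. Which filters remain, and when**

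| Filter | Provision | Wearing hours, both periods | Days 15–21 and pre-study evening |
|---|---|---|---|
| Software mode | switched off (10.1.6) | absent | absent during the study |
| Screen film | recorded only (10.1.6.5) | may be present | may be present |
| Everyday glasses | no provision | replaced by study spectacles | may be present |

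The protocol does not say what is worn on the pre-study evening. Regular glasses are the natural reading, since all participants use them daily.

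**2. Film: contrast for one child**

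Inputs: lens cut 0.40 (10.2). The sham is taken to remove nothing (assumed). The film removes a share f of screen blue light (assumed 0, 20% or 40%).

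- Light reaching the eye with the sham: 1 − f
- Light reaching the eye with the active lens: (1 − f) × (1 − 0.40) = 0.60 × (1 − f)
- Absolute contrast: 0.40 × (1 − f)

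| f | Sham | Active | Contrast |
|---|---|---|---|
| 0 | 1.00 | 0.60 | 0.40 |
| 0.20 | 0.80 | 0.48 | 0.32 |
| 0.40 | 0.60 | 0.36 | 0.24 |

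The relative cut remains 40% in every row.

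**3. Film: average over the sample**

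If a share p of children has such a film (assumed) and the effect is proportional to the light contrast (assumed), the mean effect is multiplied by k = 1 − p × f. The sample size for equal power is multiplied by 1/k².

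- p = 10%, f = 20%: k = 0.98, 1/0.98² = 1.04
- p = 25%, f = 20%: k = 0.95, 1/0.95² = 1.11
- p = 25%, f = 40%: k = 0.90, 1/0.90² = 1.23

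As a power illustration, suppose that 40 paired children would give 80% power undiluted at two-sided 5%. The standardised paired effect is then (1.96 + 0.84)/√40 ≈ 0.44. Multiplying it by k and using the normal approximation gives:

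- p = 10%, f = 20% (k = 0.98): 78%
- p = 20%, f = 40% (k = 0.92): 73%
- p = 50%, f = 40% (k = 0.80): 61%

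**4. Everyday glasses**

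During the wearing hours f = 0 from this source, so the contrast stays at 0.40. In the non-wearing period, 21 − 15 + 1 = 7 days, none is filter-free for such a child.

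**The case against.** **The lens comparison is intact for children with filtering everyday glasses.** Saliva on Days 7, 14, 28 and 35 is collected over the hours when the study spectacles are worn. This stands. A reader might infer that such glasses weaken the difference between active and sham lenses; the documents do not support that.

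**Harm through the non-wearing week needs carry-over.** Any effect would have to last to Day 28 or Day 35, when the child is on the 7th or 14th evening in the assigned lens. The documents show no such persistence, and both sequences wear regular glasses in that week. This also stands. What remains is that the week does not do its intended job for these children. The legible part of the primary analysis (14.1) does not name the pre-study sample, so its influence there is unknown.

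**Film is measured and is the same in both periods.** If left on throughout, it dilutes the difference without favouring either lens, and diary data allow it to be examined. This is correct, but recording a film does not restore the lost contrast.

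**The figures in the illustration are assumed.** Film strength and prevalence are not in the protocol. A film filters only the screen, whereas the lens also filters other light, so the loss in total evening light is smaller than 0.40 × (1 − f) suggests. Proportional response is also an assumption. The study is exploratory and sets no power target, so the sample-size multipliers have no baseline in the document. All of this stands and limits the claim about size.

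**Screening may catch such children.** The survey of the exposure environment and the physician-discretion exclusion could pick them up. Neither names filters, so this depends on who asks.

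**Conclusion.** The point holds in a limited form. The protocol protects against one kind of existing filter and leaves a second, which it recognises in its own diary item, in place during both wearing periods. For an affected child the absolute screen-light contrast falls from 0.40 to between 0.32 and 0.24, if films remove 20% to 40%. Across the trial the dilution is unknown, because the number of affected children is not given; the power and sample-size figures above only show how it would scale.

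Everyday filtering glasses are a separate and smaller matter. They make the non-wearing week, and probably the pre-study sample, not filter-free for the children who own them.

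A reader might go further and conclude that screen filters in general are kept, or that everything here pulls the result toward no effect. Neither follows. Software modes are switched off, and dilution can be argued only for films. This is an inexpensive gap to close, not a flaw that invalidates the comparison.

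**What to change.** - **Films.** Extend the instruction in 10.1.6 from night modes to blue-light-cut films on devices used before bed, to be removed from the day before Day 1 to Day 35. Ask about films in the enrolment survey of the exposure environment (10.1.6.1), because the diary starts only on Day 1 and cannot serve for screening.
- **Everyday glasses.** At enrolment, ask whether the regular glasses filter blue light. Then either do not enrol such children, through one added line in 11.1, or have them wear non-filtering glasses in the evenings of Days 15 to 21. The study's clear lens is one possibility, if masking allows.

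**Cost.** Two enrolment questions, one longer instruction and one eligibility or conduct line. Families have a little more to do, removing films departs slightly further from normal life, and the pool of eligible children may shrink somewhat. The optician visit in 16.3 is described as a check of power. Whether it can also confirm a filter is not stated, so the question to the family should not depend on it.
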